# Colorectal Chemoprevention with Calcium and Vitamin D

# [name], Dartmouth Medical School

Men and women with a recent colonoscopy in which an adenoma was removed,

with acceptable baseline measurements of calcium, creatinine and 25-(OH)-vitamin D

Three month RUN-IN period (about 3000 participants)

Randomize about 2400 men and women to:

placebo (360 men and 84 women) or

1200 mg elemental calcium (360 men and 84 women) or

1000 IU vitamin D (360 men and 84 women) or

both agents (360 men and 84 women) daily

-OR-

Randomize women who want to take calcium to:

1200 mg elemental calcium (312 women) or

1200 mg elemental calcium and 1000 IU vitamin D (312 women) daily

Subject questionnaires at 6-month intervals

Measurements of calcium, creatinine and/or 25-(OH)-vitamin D at year 1, year 3 and, if applicable, year 5

Follow-up colonoscopy at 3 or 5 years

Number and type of new colorectal adenomas found

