***5.0 Agent Information and Administration***

- 1. *Name of agents and study arms*

There will be four arms in the study:

1. placebo
2. calcium carbonate (3 gm/daily; 1200 mg elemental calcium/daily)
3. vitamin D3 (1000 IU/daily)
4. calcium carbonate and vitamin D3

*5.2 Assignment and Duration of Study Treatment*

Men will be randomly assigned to each of the treatment groups at equal frequency. Due to recommendations for high calcium intake among post-menopausal women and the common use of calcium supplements in that population group, women will have the option of being randomized to calcium or to calcium plus vitamin D (arm 2 or 4). In this way, they will receive 3 gm of supplemental calcium carbonate daily as part of the study. Based on our experience in the Aspirin-Folate Polyp Prevention Study, we assume that 35% of women will accept the full factorial randomization and 65% will wish to continue calcium supplementation and accept the restricted randomization (two arm). There will be separate randomization procedures for subjects being randomized to both agents and for women taking calcium who will be randomized only to vitamin D. Although it will not be encouraged, at any time after enrollment, women who are in the Full Factorial component of the study will have the option to change their mind and switch to the 2 Arm component of the study. Study tablets shipped to these subjects will be changed accordingly. For statistical analyses purposes they will be analyzed as per the original treatment group that they were randomized to. All randomization will be stratified by Study Center of recruitment and scheduled colonoscopic follow-up (3 years or 5 years).

The follow-up interval for colonoscopy recommended by a patient's endoscopist, either 3 or 5 years, will determine the duration of exposure to the study agents. For a 3 year follow-up interval, the duration of exposure to the study agents will be approximately two and one half years (30 months) due to the subtraction of the initial time required for subject identification and recruitment (up to four months) and a subsequent three month run-in period during which subjects take placebo pills (full factorial) or calcium alone (two arm). Likewise, the duration of exposure to the study agents will be approximately 4 and one half years (54 months) for a 5 year follow-up interval.

*5.3 Dose selection – safety and efficacy*

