Specific Aim #1: All analyses will be performed and outliers will be verified by re-assay, if urine is available. Because this is a post-hoc analysis of a randomized clinical trial and data will not be available on the entire clinical trial population, we will create a table to evaluate whether baseline characteristics are equally distributed among the participants in the sub-study. The proportion of participants in each randomized group with microalbuminuria (defined as >30 mg/g creatinine) will be compared using a chi-square test. If there are imbalances in the baseline characteristics, we will perform a logistic regression with the outcome albuminuria adjusting for characteristics that were imbalanced at baseline. In addition, we will compare medication use at follow-up to evaluate whether there were imbalances in NSAID and ACE inhibitor and Angiotensin Receptor Blocker (ARBs) use between the randomized groups.

Specific aim #2: The mean blood pressure of the 3 measurements will be used for all analyses. Baseline characteristics of the randomized groups included in this sub-study will be compared. In addition, the use of anti-hypertensive medications at the time of the blood pressure measurement will be compared between the groups. We will first compare the systolic and diastolic blood pressures among the 4 randomized groups using ANOVA. We will also compare vitamin D to no vitamin D using Student’s t-test. If characteristics are not balanced between the groups, we will use multivariable adjusted linear regression to evaluate whether treatment had an effect on systolic and diastolic blood pressures separately.

Specific aim #3: All data will be checked for outliers and specimens will be re-assayed for extreme outliers. Creatinine measurements will be converted to estimated glomerular filtration rates using the CKD-Epi equation. [188](#_ENREF_188) We will compare the prevalence of CKD (defined as an estimated GFR <60 ml/min/1.73m2) between the 4 treatment arms using chi-square test. We will also used random effects models with repeated creatinine measures which can account for missing values to compare serial creatinines between the 4 treatment groups. To evaluate whether calcium and/or vitamin D supplementation over 5 years affected serum phosphate, alkaline phosphatase, intact PTH and FGF-23 levels, we will compare levels between the intervention groups and the placebo group using appropriate methods for skewed data.

*10.6.7 Human Subjects Research*

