### 13.5 Statistical Analysis

All analyses will be conducted according to the principle of intention to treat. The analysis population will consist of all randomized patients, with patients being grouped according to randomized treatment assignment regardless of whether this treatment was actually delivered.

To address our primary hypotheses, the primary statistical analysis will use contingency tables and standard 2 tests to compare adenoma occurrence between treatment groups. There will be three primary comparisons: 1) vitamin D versus no vitamin D, and 2) calcium versus no calcium and 3) vitamin D + calcium versus calcium alone. Comparison 1 will collapse numbers of subjects across calcium supplementation groups to assess the marginal effect of vitamin D. Comparison 2 will collapse numbers of subjects across the vitamin D supplementation groups to assess the marginal calcium effect and will exclude women who do not consent to randomization in the calcium component of the study. Comparison 3 will focus only on subjects taking calcium; no collapsing is necessary. Effects will be summarized using risk ratios rather than odds ratios to improve interpretation. Two-sided significance levels of 0.05 will be taken to denote statistical significance.

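### The kidney sub-study compares outcomes across all four arms without the full-factorial restriction that the main trial uses, so its calcium contrasts are only partly randomised

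*Protocol*

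**What the plan says.** Section 10.6.6 sets out the tests for the kidney sub-study:

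- Aim 1: "The proportion of participants in each randomized group with microalbuminuria" is compared by a chi-square test. Logistic regression follows if baseline characteristics turn out imbalanced.
- Aim 2: the plan is first to "compare the systolic and diastolic blood pressures among the 4 randomized groups using ANOVA", then to compare vitamin D with no vitamin D by t-test. Adjusted linear regression follows if characteristics are not balanced.
- Aim 3: CKD prevalence (eGFR below 60) is compared over the four arms by chi-square. Random-effects models are used "to compare serial creatinines between the 4 treatment groups". Phosphate, alkaline phosphatase, PTH and FGF-23 are compared between the intervention groups and placebo. No adjustment, stratification or restriction is stated for any of these.

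On the design, section 5.2 says that "women will have the option of being randomized to calcium or to calcium plus vitamin D (arm 2 or 4"). The schema in section 3.2 gives the planned numbers: "placebo (360 men and 84 women) or" for placebo, the same for vitamin D alone, and "1200 mg elemental calcium (360 men and 84 women) or" for the factorial part of the calcium arm, with the same again for both agents. A further "1200 mg elemental calcium (312 women) or" enter calcium alone, and as many enter calcium plus vitamin D.

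Section 13.5 deals with this in the main trial. The calcium comparison "will exclude women who do not consent to randomization in the calcium component of the study", and the interaction test is limited to the full factorial.

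**The concern.** The four arms are not four random samples of one population. Two of them hold a large block of women who chose calcium and could never have been assigned to the other two. A comparison of either calcium arm with placebo or with vitamin D alone therefore mixes the effect of calcium with sex and with whatever distinguishes women who want to keep taking calcium. A four-arm test does the same.

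This touches a stated hypothesis. Section 10.6.2 predicts better kidney function with vitamin D and calcium than with placebo, which sets an arm that is about half women against one that is about one fifth women. Section 6.3.2 itself treats sex as relevant to creatinine, since it doubts reference ranges that ignore it. If levels are compared, the sex mix would favour calcium and could offset a true rise.

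**Working it through.** **Inputs.** 2400 randomised, 60% men and 40% women (section 13.2). 35% of women in the full factorial and 65% in the two-arm component (section 5.2). About 900 participants for urine and blood pressure and about 1500 for creatinine, with a creatinine target of 0.1 mg/dL at 90% power (section 10.6.5). The documents give neither a male-female creatinine difference nor a creatinine SD; both are assumed below.

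**Reproducing the schema.**
- Men per arm: 2400 × 0.60 / 4 = 360.
- Full-factorial women per arm: 2400 × 0.40 × 0.35 / 4 = 84.
- Two-arm women per calcium arm: 2400 × 0.40 × 0.65 / 2 = 312.

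All three match section 3.2.

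**Composition of the arms.**

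| | Men | Women | Total | Women | Elected calcium |
|---|---|---|---|---|---|
| Each non-calcium arm | 360 | 84 | 444 | 18.9% | 0% |
| Each calcium arm | 360 | 84 + 312 = 396 | 756 | 52.4% | 312/756 = 41.3% |

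The gap in the share of women is 33.5 points. With the 37% women reported in section 10.6.7.a and the same 35/65 split, the shares are 17.1% and 49.2%, a gap of 32.2 points.

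**Creatinine, if levels are compared.** Bias under no treatment effect = gap in share of women × male-female difference.

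| Assumed male-female difference (mg/dL) | Calcium arms lower by (mg/dL) | As a share of the 0.1 target |
|---|---|---|
| 0.10 | 0.335 × 0.10 = 0.033 | 33% |
| 0.15 | 0.050 | 50% |
| 0.20 | 0.067 | 67% |
| 0.25 | 0.084 | 84% |

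**The same bias in standard errors.** With 1500 subjects, the calcium arms hold 945 and the others 555, so SE = SD × √(1/945 + 1/555) = 0.0535 × SD. Read as a simple two-group comparison, the power statement in 10.6.5 implies SD = 0.1 / [(1.96 + 1.28) × √(2/n)]. This is about 0.60 for 750 per group and about 0.42 for 375 per group.
- SD 0.60: SE 0.032, so the bias is 1.0 to 2.6 standard errors.
- SD 0.42: SE 0.022, so the bias is 1.5 to 3.7 standard errors.

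**Creatinine, if change from baseline is tested.** A constant sex difference in level cancels. What remains is mainly any difference in course between women who elected calcium and everyone else. The documents give no figure for it.

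**Cost of restricting.** 1776/2400 = 74% of subjects stay: about 666 of 900 and 1110 of 1500. The creatinine comparison becomes 555 against 555, and the standard error rises by √(2/555) / √(1/945 + 1/555) = 1.12. Women are then 18.9% of every arm and the sex-mix bias is zero.

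**The case against.** Much of the case on the other side stands, and it rules out three stronger readings.

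*That every calcium contrast is confounded by sex.* Section 10.6.6 adjusts microalbuminuria and blood pressure when baseline characteristics are imbalanced. A gap of more than 30 points in sex among 900 people would be seen, so sex would very probably enter those models. Randomisation component is not named as a covariate, so self-selection can remain. For creatinine, section 10.6.5 speaks of evaluating changes, and a group-by-time test would cancel a constant sex difference; 10.6.6 does not say which effect is tested. CKD is defined on eGFR, so the mg/dL arithmetic does not carry over to it.

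*That a false creatinine difference is close to certain.* An SD of 0.2 mg/dL would put the bias at 3 to 8 standard errors. That SD is not in the protocol and does not fit its power statement, which implies roughly 0.4 to 0.6 on a two-group reading and hence about 1 to 4 standard errors.

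*That the analysis could hide the finding behind the October 2011 unanticipated-problem report.* The protocol describes the follow-up procedures but not what the report found. Monitoring of individuals does not depend on 10.6.6: section 6.3.2 uses each person's own rise from baseline, and the monitoring committee reviews adverse events every six months.

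It is also fair that the primary kidney hypothesis concerns vitamin D, which is randomised in both components, and that this is an ancillary analysis. Model covariates can be left to an analysis plan. But comparing all four arms is a choice 10.6.6 states, and it departs from 13.5.

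**Conclusion.** The point holds in limited form. As written, 10.6.6 yields calcium and four-arm contrasts that are not fully randomised, because 41% of each calcium arm elected calcium and the share of women is 52% against 19%. Those figures follow from the protocol's planned numbers and need no outside assumption.

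The exposure differs by outcome. For microalbuminuria and blood pressure, mainly self-selection by component is left after the conditional adjustment. For creatinine, CKD and the end-of-treatment markers, no adjustment is stated. The creatinine bias of 0.03 to 0.08 mg/dL requires both that levels are compared and that men are 0.10 to 0.25 mg/dL higher; neither is given in the document. No bias size can be derived for the other outcomes. This problem does not affect vitamin D versus no vitamin D, nor the main trial's calcium and interaction analyses. Severity is moderate.

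**What to change.** Amend section 10.6.6 as follows:

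1. Limit calcium versus no calcium, all four-arm tests, and comparisons of individual arms with placebo to full-factorial participants, classified by component at randomisation, for all kidney outcomes. This follows 13.5.
2. Keep all participants for vitamin D versus no vitamin D, with randomisation component and sex as covariates.
3. Name vitamin D versus no vitamin D as the aim-1 test. The aim-1 hypothesis in 10.6.2 and the microalbuminuria power statement in 10.6.5 both concern vitamin D, whereas 10.6.6 gives that contrast explicitly only for blood pressure.
4. State whether the creatinine model tests level or change over time.

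The cost is wording. Calcium contrasts keep about 74% of subjects, with a standard error about 1.12 times larger for creatinine; vitamin D contrasts lose no one.

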# *10.7.2 Objectives*

# Using data already collected during the trial (Section 5.15), we will:

# 1. Identify symptoms and other predictors of subsequent allocation belief at randomization, year 2, and end of treatment (EOT).

# 2. Assess how subjective and objective health outcomes are affected by allocation beliefs, efficacy beliefs, and preference.

# 3. Assess the effects of allocation beliefs, efficacy beliefs, and preference on adherence.

*10.7.3 Data collection*

Data collection (approved previously) is conducted as part of the routine interviews for the parent study, as well as separate mail-back study methods surveys.

*10.7.4 Analyses*

Allocation beliefs will be classified as “Believe Active” (A) for any active treatment option in the 4-arm study or calcium+vitamin D in the 2-arm study;. “Believe Placebo” (P) for placebo in the 4-arm study; calcium in the 2-arm study; or “Don’t Know (DK). We will analyze all subjects, and separately those in the 4-arm and 2-arm studies. We will assess the distribution of forced guesses of those who said DK and incorporate the appropriate analyses and sensitivity analyses to show the effect of pooling forced guesses with Active or Placebo guesses. A 2-sided p-value <0.05 will be considered statistically significant. We will not adjust for multiple testing. Our analyses will be based primarily on describing the data and regression modeling..

Aim 1. Identify predictors of allocation belief at randomization, year 2, and EOT.

At different times during the trial, we will classify the reasons subjects provided for their allocation beliefs and explore the factors that predict beliefs. We will explore the factors associated with misunderstanding of equipoise and randomization.

Hypothesis 1. Allocation beliefs change during the course of a double-blinded trial. We will describe the distributions of beliefs, changes in beliefs from randomization to year 2 [EOT], and use regression models to identify factors related to changes of belief.

Aim 2. Examine how subjective and objective health outcomes are affected by allocation beliefs, efficacy beliefs, and preference.We will assess how beliefs affect subsequent symptoms and on colorectal adenoma, using multivariable regression.

Hypothesis 2a. Allocation beliefs at randomization [year 2, EOT] predict the occurrence of each of five specified health effects, after adjustment for a history of that same health effect. We will use multivariable regression models of the relations between beliefs and subsequent symptoms identified during routine bi-annual telephone surveys.

Hypothesis 2b. Allocation beliefs at randomization [year 2, EOT] predict a significant change in each of five SF-36 scores during the study, independently, or by interaction with efficacy beliefs about that health effect, after adjusting for baseline score and randomized treatment. Hypothesis 3 is analogous to Hypothesis 2, but uses SF-36 data on general health, physical functioning, bodily pain, vitality, and mental health.

Aim 3. Examine how adherence is affected by allocation/efficacy beliefs, and preference.

We will model subjects’ adherence, in relation to their preferences, efficacy beliefs, and allocation beliefs at different times, and demographic and medical factors.

Hypothesis 3. The proportion of pills taken during run-in is associated with allocation beliefs at randomization, after adjustment for baseline efficacy beliefs and preferences. We will develop a model for adherence including allocation belief; efficacy belief, preference, and repeat these analyses for adherence averaged over the first two years. We will develop models to predict completion of the trial on study pills.

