In a randomized placebo-controlled trial, the validity of the results depends on the effectiveness of methods to blind participants to the randomization assignment. Unblinding is a potential source of bias because someone who believes they are getting the active treatment may experience or report better outcomes. To assess unblinding, this study includes a longitudinal evaluation of blinding effectiveness as well as an assessment of the effect of participants' beliefs about the intervention on measured and self-reported health outcomes in each intervention arm.

Participants will be asked at Intake which pill they would prefer to receive if they had a choice. They will also be asked to describe their beliefs about the efficacy of calcium and vitamin D in relation to general health, prevention of colorectal polyps, and improvement of mood, depression, constipation, and bone and joint pain. After the run-in period they will be asked to guess which pill they think they have received and the reasons for their guess. In addition, subjects will be asked to complete two more questionnaires, by mail or telephone interview, at the end of year 2 and at the time of the participants' follow-up colonoscopy (Year 3 or 5). These questionnaires will be administered by independent staff from Geisel School of Medicine at Dartmouth and not by the study coordinators, because the coordinators help to collect endpoint data and could be biased by participants' responses.

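### The belief coding in 10.7.4 treats every active guess alike in the 4-arm component, so it cannot show agent-specific belief or unblinding, and pooled models need a component term

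*Protocol*

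**What the plan says.** Section 10.7.4 (Analyses) sets a three-way code for allocation belief. A participant is Active (A) "for any active treatment option in the 4-arm study or calcium+vitamin D in the 2-arm study", and Placebo (P) "for placebo in the 4-arm study; calcium in the 2-arm study; or" else Don't Know (DK). Two analyses follow directly: "We will analyze all subjects, and separately those in the 4-arm and 2-arm studies". Forced guesses from the DK group are to be examined, with "sensitivity analyses to show the effect of pooling forced guesses with Active or Placebo guesses".

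The raw answer is finer than this code. Section 5.15 states: "After the run-in period they will be asked to guess which pill they think they have received and the reasons for their guess". It also records "beliefs about the efficacy of calcium and vitamin D in relation to general health, prevention of colorectal polyps, and improvement of mood" and several symptoms.

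Hypothesis 2b relates allocation belief to change in SF-36 scores, alone or in interaction with efficacy beliefs. It names two adjustment variables: the starting score and the allocated treatment. The primary comparisons in 13.5 are vitamin D v none, calcium v none, and both agents v calcium alone.

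**The concern.** Section 5.15 ties the validity of the results to effective blinding. In a factorial trial the useful question is asked agent by agent: do those given calcium come to think they take calcium, and likewise for vitamin D? A code that merges the three active answers cannot address this within the 4-arm component, which is most of the trial. Running the 4-arm component separately does not help, because the merging happens inside it.

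The pooled analysis raises a second issue. The same stated belief, calcium only, falls on different sides of the A/P split in the two components, and the 2-arm component consists only of women. An association between A/P and an outcome in the pooled data could partly reflect which component, and which sex, a participant belongs to.

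**Working it through.** The plan gives no figure for this point, so there is none to reproduce. The check applies the stated code to the planned sizes.

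**Inputs.** Planned randomised numbers (13.2 and the 3.2 schema): 4-arm 1776 (444 per arm; 1440 men and 336 women), 2-arm 624 women (312 per arm). Section 10.7.4 (Sample size) cites 2,259 actually randomised but gives no split by component, so the planned sizes are used.

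**1. The code, side by side**

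| Guess | 4-arm | 2-arm |
|---|---|---|
| Placebo | P | no code given |
| Calcium only | A | P |
| Vitamin D only | A | no code given |
| Both | A | A |

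In the 2-arm component A v P is exactly the vitamin D guess, so nothing is hidden there. In the 4-arm component three different beliefs share one code.

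**2. Can the 4-arm code detect agent-specific unblinding?** Suppose that all placebo participants guess placebo, and compare two patterns in the active arms.

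| Assigned arm | Coded A if active arms guess at random among the three active pills | Coded A if each identifies its own pill |
|---|---|---|
| Placebo | 0% | 0% |
| Calcium | 100% | 100% |
| Vitamin D | 100% | 100% |
| Both | 100% | 100% |

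The tables are identical, so the code cannot tell the two patterns apart.

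**3. What A and P contain when pooled.** Assume uniform guesses over the options in each component and no DK.

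- Chance of A: 3/4 = 75% (4-arm) and 1/2 = 50% (2-arm). Pooled: (1776 × 0.75 + 624 × 0.50)/2400 = 1644/2400 = 68.5%.
- Calcium-only guesses: 1776 × 0.25 = 444 coded A, and 624 × 0.50 = 312 coded P.
- Of 1644 coded A, 444 (27%) believe they get no vitamin D.
- Of 444 + 312 = 756 coded P, 312 (41%) believe they take calcium.

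**4. Confounding by component.** Under the same assumption, 2-arm women are 312/1644 = 19.0% of A and 312/756 = 41.3% of P. If belief has no effect, but the outcome still differs by δ between components after the other adjustments, the pooled P v A contrast shows (0.413 − 0.190) × δ = 0.22δ. The documents give no δ. Over an assumed range of 0.1 to 0.5 SD, the spurious contrast is 0.02 to 0.11 SD. Component is also closely tied to sex: women are 336/1776 = 19% of the 4-arm component and 100% of the 2-arm.

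**The case against.** Much of the case for the plan stands.

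- **The code has a coherent meaning.** A reader might infer that coding calcium only as A in one component and P in the other makes the variable self-contradictory. The documents do not support that. Every 2-arm woman knowingly receives calcium and only vitamin D is randomised, so calcium only is her component's comparator. A reads as belief in a randomised active treatment, and P as belief in the comparator, in both components.
- **The code fits the first guess.** During run-in the 4-arm participants took placebo and the 2-arm women took calcium alone (5.2). P is then the pill actually taken. Comparing that guess with assignment would be meaningless, since no randomised agent had been taken and 2,813 − 2,259 = 554 enrollees were never randomised.
- **Safeguards are stated.** DK is kept as its own category, forced guesses are examined, and each component is also analysed alone. Aim 3 mentions demographic factors, so sex may enter the adherence models. An analysis plan that is not shown could add component elsewhere.
- **Section 10.7 lists no comparison of guess with assignment.** Section 5.15 announces a separate evaluation of blinding. It gives no agent-level method, however, and 10.7.2 draws on the same answers.

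Three further inferences should be resisted. The 624 in the 2-arm component are not all holders of a calcium-only belief; 624 is the whole component, and the number with that belief is unknown. The agent-level guesses are not lost, because they remain in the collected data. Nor does the protocol call constipation or bone pain specific to one agent: 5.15 lists them for calcium and vitamin D together, and the questionnaire that would show whether efficacy beliefs were asked per agent is not available.

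None of this restores the distinction between agents inside the 4-arm component, and a coherent definition of A and P does not remove confounding by component.

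**Conclusion.** The point holds as a minor one. Within the 4-arm component, the A/P/DK code cannot separate belief in calcium from belief in vitamin D. It therefore cannot show agent-specific unblinding or agent-specific belief effects. This follows from the stated rule and needs no assumption.

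In the analysis of all subjects, A v P differs in meaning and in chance rate by component, so pooled belief-outcome associations can be confounded by component and sex. The 75% v 50% chance rates and the 0.22δ contrast rest on uniform guessing with no DK, and the actual size depends on guesses and outcome differences not given in the protocol. Hypothesis 2b's adjustment for allocated treatment would cover component only if the 4-arm and 2-arm calcium groups were kept as distinct treatment levels; 5.1 lists four arms. Adjusting for the starting score may remove part of the confounding.

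The analysis is ancillary and largely descriptive. No primary comparison uses it, and the study pathologist reads the endpoint without knowledge of assignment (8.0).

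**What to change.** - Keep the A/P/DK variable.
- From the same answers, derive two more, each yes/no/DK: believes receiving vitamin D (all subjects) and believes receiving calcium (4-arm only).
- At year 2 and end of treatment, compare each with assignment to that agent. Do not do this for the guess made after run-in.
- Include component (4-arm v 2-arm) as a term in every pooled belief model.

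The cost is recoding of answers already collected, with no new data. The downside is a few more terms and tests in an ancillary analysis that makes no multiplicity adjustment, so the added results should be read as descriptive.
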